## Abstract

**Background:**

Obesity is an increasing health concern in Australia among adult and child populations alike and is often associated with other serious comorbidities. While the rise in the prevalence of childhood obesity has plateaued in high-income countries, it continues to increase among children from disadvantaged and culturally diverse backgrounds. The family environment of disadvantaged populations may increase the risk of childhood obesity through unhealthy eating and lifestyle practices. The Strong Families Trial aims to assess the effectiveness of a mixed behavioural and lifestyle intervention for parents and carers of at-risk populations, i.e. families from culturally diverse and disadvantaged backgrounds, in preventing unhealthy weight gain among children aged 5 to 11 years.

**Methods:**

Eight hundred families from low socio-economic areas in Greater Western Sydney, NSW, and Melbourne, VIC, will be recruited and randomised into a lifestyle intervention or control group. The intervention comprises 90-minute weekly sessions for 6 weeks (plus two-booster sessions) of an integrated, evidence-based, parenting and lifestyle program that accounts for the influences of family functioning. Primary (anthropometric data) and secondary (family functioning, feeding related parenting, physical activity, consumption of healthy foods, health literacy, family and household costs) outcome measures will be assessed at baseline, immediately following the intervention, and 12 months post-intervention.

**Discussion:**

This study will elucidate methods for engaging socially disadvantaged and culturally diverse groups in parenting programs concerned with child weight status.

**Trial Registration:**

This study is registered with the Australian New Zealand Clinical Trials Registry (ACTRN12619001019190). Registered 16 July 2019.

## Background

Childhood obesity is a serious public health problem that tracks from early childhood into adulthood [1, 2]. While the prevalence of childhood obesity has plateaued in most high-income countries, [3] it continues to increase among children from disadvantaged and culturally diverse backgrounds [4–6]. Little attention has been given to trialling interventions to reduce unhealthy weight gain among children from disadvantaged and culturally diverse backgrounds, [7, 8] despite data suggesting that even small reductions in body mass index (BMI) are associated with improvements to cardiovascular risk factors in children [9]. This is a significant issue, since children living in areas with the lowest socio-economic status (SES) are at higher risk of being affected by overweight or obesity than those living in higher SES areas [10–12]. A systematic review of 45 studies found that social disadvantage was associated with increased odds of childhood obesity. Specifically, there was an identified inverse association between adiposity in children and SES in 19 studies (42%) [13]. Moreover, the magnitude of associations between SES and adiposity were further analysed in 24 studies, in which 21 of those found a significant inverse SES-adiposity association [13]. The odds ratio for adiposity in lowest SES children, when compared to highest SES children, ranged from 1.3-6.7, with a median odds ratio of 2.04 [13].

It has been postulated that the family environment of disadvantaged populations is one of several behavioural factors that increase the risk of obesity through unhealthy eating and lifestyle practices [14–17]. The impact on weight status of physical inactivity and corresponding high levels of sedentary behaviour, high energy density diet and other poor dietary and lifestyle choices are well documented, [18–20] and these factors are a particularly impacted by the family environment [14, 15]. Disadvantaged households are more likely to experience conflict, communication difficulties and disengagement, which collectively may affect children’s health including body weight [14]. Therefore, health behaviours are learned within, and shaped by, the family environment. For example, previous studies have shown that family functioning is independently associated with obesity among parents and their offspring, with the prevalence of poor family functioning increasing from 22% to 29% and as high as 39% as the number of obesity risk behaviours increases from 0 to 1 and then 2 or more, respectively [14, 15]. Family social disadvantage affects children’s weight by restricting access to financial, social and educational resources that support children’s healthy development and impacts family functioning [14, 15]. Moreover, low family cohesion, high family conflict, and inadequate social support make it difficult for parents to provide optimal environments for shaping healthy eating habits and physical activity [21]. Consequently, parents have difficulty managing family meals and routines, healthy lifestyles, parenting roles, communication with family members and maintaining social supports [14, 15]. Previous work in this area identified that poor family functioning and parental psychological distress were significantly associated with increased consumption of unhealthy foods among primary school children [21]. It has been estimated that poor family functioning accounts for 14–24% of the variance in BMI among children and adolescents in disadvantaged populations [14, 15].

Behavioural parenting interventions are grounded in learning theory with a focus on teaching parents how to respond empathically to children’s needs [22, 23]. Such approaches result in improved parenting, an understanding of risk and protective factors for children’s healthy development, and increased family cohesion [14]. Behavioural parenting interventions can be alternative approaches to obesity prevention when they address the family environment’s influence upon child weight status, and have potential for translation into health and community service delivery [14]. Findings from such interventions targeting infants and pre-school children, and aiming to improve eating and physical activity patterns, suggest that family focused interventions may also have potential for prevention of unhealthy weight gain, [24–26] with significant intervention effects for a number of maternal feeding practices and child BMI-for-age Z-score (BMIz score) [27]. Studies on fundamental family dynamics of communication, conflict resolution and parent–child engagement are scarce. To date, there have been limited Australian trials of family-focused obesity prevention programs among disadvantaged multi-ethnic families for primary school- aged children.

A series of pilot studies were conducted, which focused on African migrant families with children aged 12-17 years (Healthy Migrant Families Initiative), [17, 28] featuring a two-part intervention. The first focused on healthy eating, active living and healthy body weight, and the second focused on parenting, communication and problem solving [17]. The pilot studies were favourably received as an obesity prevention program among African migrant communities and provided the foundation for the present study. The pilot data was also consistent with other data from Australia and the United States, indicating that children over 5 years of age have a higher prevalence of overweight and obesity compared to children under 5 years [12, 29]. Specifically, the obesity prevalence in the United States among 6- to 11-year-olds in 2017-2018 was 20.3% compared to 13.4% among 2- to 5-year-olds [29]. In Australia, more than 1 in 5 children (24%) aged between 5 and 16 years of age were overweight or obese in 2018 [12]. Furthermore, overweight and obesity prevalence is slightly higher among 5- to 11-year-olds (25.1%) compared to 12- to 16-year-olds (22.5%) [12]. The age group of children prior to adolescence also represents a time of relative stability in a child’s life, when parents are still the major providers of a child’s eating and physical activity environment. For example, in children under 12 years of age approximately 70% of a child’s food is consumed in the home environment and therefore constitutes a major determining factor of a child’s weight trajectory over time [30]. Family functioning, parenting skills training, positive family relationships, healthy lifestyle (nutrition and physical activity) were the key intervention priorities identified. Therefore, the current trial builds on previous research and focuses on evaluating the effectiveness of an integrated package of parenting and lifestyle interventions in preventing unhealthy weight gain and improving the family environment among disadvantaged populations that carry the highest burden of childhood overweight and obesity. It also aligns with advice from the World Health Organization and United Nations Children’s Fund, that acknowledges that reduction and prevention of overweight and obesity in children and adolescents requires a comprehensive and supportive approach, targeting lifestyle and behavioural change [31, 32]. The trial is timely because the COVID-19 and pandemic lockdowns have had an impact on family functioning, intergenerational communication, social isolation and feelings of loneliness [33]. Moreover, such impacts of COVID-19 and lockdowns have been associated with decreased physical activity, poorer nutrition, rises in screen behaviours and food insecurity and shortages, which are estimated to be reversing the obesity plateauing gains [34].

The primary hypothesis is that improving family functioning among parents or carers of 5 to 11-year-old children from disadvantaged backgrounds will reduce BMIz score immediately following the intervention, and 12-months post-intervention, relative to a control group. The secondary hypotheses (immediately following the intervention and 12-months post-intervention when compared to the control group) include:The percentage of intervention group families functioning poorly and experiencing parenting-related intergenerational conflicts will be decreasedThe percentage of intervention group families eating a family meal together and adopting healthy dietary practices will be increasedAmong parents and their 5 to 11-year-old children, the mean duration of time spent in physical activity will increase, and screen viewing time will decreaseThe percentage of intervention group parents with adequate knowledge regarding healthy lifestyles (healthy food and dietary choices, healthy eating, physical activity, and sedentary behaviours) will increaseThe self-efficacy of these behaviours in children aged 5 to 11 years will be greater in intervention families than the control group following the intervention program

## Methods

### Study design

The Strong Families Trial will employ a cluster randomised control trial (RCT) design to evaluate the effectiveness of an integrated package of parenting and lifestyle interventions parents and carers of 5 to 11-year-old children in preventing unhealthy weight gain and improving the family environment among disadvantaged culturally diverse populations. The study will evaluate whether a behavioural parenting and lifestyle program consisting of 6 x 1.5-hour weekly group sessions (plus 2 boosters at 3 months post intervention) is effective, sustainable and cost effective in improving children’s anthropometric outcomes. Measurements will be made at baseline (0 weeks), at the end of the 6-week intervention (10 weeks), and at 12-months post-intervention (60 weeks). Details of the study timeline and an overview of methods, randomisation and allocation to groups are shown in Fig. 1 and outlined in the following sections. Briefly, potential participants will be directed to a survey online (trial website), where they can register their interest in the study. Eligible participants will then undergo phone screening to further assess their eligibility and willingness to partake in the Trial. Once enrolled, participants will be assigned to a bilingual field worker for baseline testing and then randomly assigned to the intervention or control group.

**Fig. 1 Fig1:**
[figure not shown]
Study design and schedule of enrolment, interventions, and assessments for the Strong Families Trial

### Design and study setting

The trial will use a cluster RCT design with the primary unit of randomisation being postcode of address. This community-based cluster RCT trial will be conducted in the most disadvantaged areas of Greater Western Sydney and Greater Melbourne, with Index of Relative Socio-Economic Disadvantage (IRSD) score of <1000, the cut-off used to indicate socio-economic disadvantage [35]. IRSD is one of four indices of the Socio-Economic Indexes for Areas (SEIFA), developed by the Australian Bureau of Statistics as a measure of socio-economic conditions according to geographical areas. The indices are derived from information obtained during the five-yearly national Census [36]. As at the 2016 Australian population census, the project area has 398 postal areas (POAs) in Greater Western Sydney [37] and Greater Melbourne [38] with a usual resident population of 6,812,614 [39]. Of those, 105 POAs have an ISRD <1000 with a usual resident population of 2,502,846. Of the 105 POAs, 92 have at least 1% of the population speaking Chinese, Arabic, Hindi, Vietnamese, Hindi, or Punjabi at home [40]. In the 92 POAs, 29.6% of households (*n*=131,180) in Greater Western Sydney and 25.2% of households (*n*=120,411) in Greater Melbourne are families with children under 15 years of age [41]. These 92 postcodes will be purposively sampled and included in the study as the targeted population, on the basis of ISRD <1000, >1% of the population speaking one of the languages of interest at home, and having a significant percentage of families with children under the age of 15.

### Participants

Study participants will include 800 families (children aged 5-11 years and their parents/carers) at risk of unhealthy weight gain.

### Recruitment

Methods of recruitment employed in the trial will include flyer distribution, school recruitment, community databases and social media campaigns. The trial flyer will be delivered in each of the languages included in the study (English, Arabic, Vietnamese, Chinese, Hindi and Punjabi) and will be distributed by local community contacts working closely with communities of interest either electronically via email or face-to-face through hard copies. Primary schools (government and non-government) in the study area will be engaged to promote the trial to their school population. Schools will be provided with the trial flyer and a condensed excerpt suitable for inclusion in a newsletter. Approval will be sought from the relevant education bodies. Social media platforms (Facebook, Instagram) will also be used for recruitment purposes, through a paid social media campaign within Western Sydney University. The advertising will target parents from relevant geographical areas with children between 5- to 11-years-of-age and culturally diverse parents of interest. The social media campaign will direct interested participants to the study website (www.westernsydney.edu.au/strongfamiliestrial) for further information. The website will serve as the primary method for interested participants to receive information about the study and submit an expression of interest in participating. Other forms of recruitment that will be used include promoting the study via email and trial flyers in community healthcare centres, contacts and noticeboards; health professionals such as family medical practitioners, paediatricians and dietitians; language or migrant resource centres; and places of worship.

The study will use the Research Electronic Data Capture (REDCap) [42, 43] licensed software to assess the eligibility of interested participants, confirm participant details, track progress and manage participant data. Potential participants enquiring about the study will fill in an online survey for screening purposes through the REDCap software, which will then be followed up by phone screening with research staff to assess eligibility for the study and record participant contact and personal details on the eligible adult and child. Once accepted into the study, the participant will be assigned to a bilingual field worker for baseline assessment.

### Eligibility

Potential participants will be screened for eligibility according to the following inclusion and exclusion criteria:

#### Inclusion criteria:

Families (parent- or carer-child dyad) who live in the Greater Western Suburbs of Sydney or Western and Northern Suburbs of MelbourneParents who live in the same household as their child aged between 5 to 11 yearsFamilies who are socio-economically disadvantaged (<1000 Index of Socio-Economic Disadvantage)For households with two or more eligible children, the child who had the most recent birthday will be included.

#### Exclusion criteria:

Self-reported mental or major physical illness or intellectual disability among parents/carers and/or their eligible offspring which would hamper effective participation and/or lead to inability to commit to the group process.

### Outline of trial procedure

Families (parent- or carer-child dyad) with 5 to 11-year-old children in selected suburbs of Greater Western Sydney and Greater Melbourne will be identified, screened and randomly allocated to behavioural parenting and lifestyle program intervention or control. Measurements at baseline (timepoint 1; T1 = 0 weeks), end of intervention (timepoint 2; T2 = 10 weeks) and 12 months post-intervention (timepoint 3; T3 = 60 weeks) will assess changes in children’s weight, height, physical activity, and eating behaviours, as well as in family functioning, parental knowledge and behaviour. Participation in the study will be entirely voluntary and participants will be free to withdraw at any time.

### Assessment

Children’s anthropometric data (primary outcomes) will be measured at 0, 10 and 60 weeks by bilingual field workers to assess the changes weight gain. Measurements will include the child’s height and weight according to a standardised protocol. All bilingual field workers will receive appropriate training by research staff prior to collecting data from research participants. Each field worker will also receive an equipment kit with a detailed instruction manual, height and weight measurement guide, and other necessary items to collect participant data. Parents or carers (of the parent- or carer-child dyad) will participate in a face-to-face interview with trained bilingual field workers to collect data on family functioning, feeding related parenting, physical activity and consumption of healthy foods of the participating child, parents’ health literacy, and family and household costs (secondary outcomes). The following outcome measures will be collected via face-to-face survey using Qualtrics software (Qualtrics, Provo, UT):Study specific questionnaire to capture socio-demographic dataFamily Functioning using the McMasters Family Assessment Device [44].General Parenting Questionnaire as a composite measure of general parenting behaviours/practices and constructs (sense of competence/efficacy)Feeding related parenting will be measured using the Child Feeding Questionnaire [45].Child's Health-related quality of life will be measured by the Child Health Utility 9D [46–49].Parent-reported participation in sports and other physical activity, measured using 1 item from the NSW Population Survey 2019 [50].Child adherence to physical activity guidelines will be assessed using a composite measure of parent-reported accumulated moderate to vigorous physical activity (MVAP) of at least 60 minutes per day in 2 reference periods (past 7 days and a typical week).Leisure-time sedentary behaviours of children will be assessed using parent-reported time spent in sedentary recreational screen time (i.e. television, seated electronic games and electronic device use other than for schoolwork) in a typical week. It will be a composite measure using 1 item from the Sax Institute Short survey instruments for children’s diet and physical activity, [51] and 1 item from the Youth Risk Behaviour Surveillance System [52].Consumption of healthy foods will be measured by items from the Child Component NSW Population Health Survey 2007-2008, [53] National Health Survey 2017-2018 [54] and Short survey instruments for children’s diet (the Sax Institute for the NSW Ministry of Health) [51].The Strengths and Difficulties Questionnaire [55] will be used to measure socio-emotional problems.Parental health knowledge will be measured using the Lifestyle & General Nutrition Knowledge Questionnaire [56].Participant Evaluation Questionnaire as a composite measure to assess satisfaction with intervention.

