### Blinding

All bilingual field workers will be blinded to randomisation and will therefore have no knowledge of which group (intervention or control) the participating parent- or carer-child dyad has been allocated to. Group facilitators are unable to be blinded to randomisation given the nature of the intervention but will only be assigned after baseline data collection has been completed. Furthermore, they will take no part in data collection and will only be involved in the delivery of their designated intervention modules. Research staff will not take part in data collection.

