### Statistical analysis

Data on socio-demographics, anthropometry, general parenting, feeding-related parenting, child’s health and quality of life, physical activity and consumption of healthy foods, parents’ health knowledge and health and household costs will be collected. Child’s anthropometric measurements will be taken at baseline, at completion of the intervention and 12 months after completion of the intervention. Height and weight of the participating child will be used to calculate the BMIz score (primary outcome measure) [57, 58]. Cost per BMIz saved and incremental cost per quality-adjusted life-year gained will also be calculated (Incremental cost per quality-adjusted life-year gained at baseline, end of intervention and 12 months following intervention). Parents will respond to self-administered questionnaire on family functioning, feeding related parenting, physical activity and consumption of healthy foods of the participating child, parents’ health literacy, and family and household costs. The analysis will follow an intention-to-treat approach and with supplementary per protocol analysis. Research data will be analysed with Stata 16 [59]. The statistical analysis will use a modelling approach that aims to capture the profile of the intervention group compared to the control group and while accounting for potential unobserved differences between the intervention and control groups that (if not accounted for) could bias results. The models will evaluate the impact of the interventions over time by testing for an interaction between time and intervention group. This will be followed by multivariable linear models after adjusting for baseline characteristics and other variables (standard demographic variables such as age, sex, income, education, and SEIFA). Subgroup analysis will be undertaken for within-intervention group differences between English speaking and Non-English-speaking groups. Model assumptions will be checked and appropriate adjustments to the analysis made where necessary. A *p*-value <0.05 will be considered statistically significant. The cost-effectiveness analyses will be conducted to determine incremental cost per quality adjusted life year gained by comparing the direct costs and outcomes of behavioural parenting and lifestyle program over usual care from a health care perspective at completion of the intervention and at 12 months post-intervention. The within-trial analysis will adopt a micro-costing approach to calculate the costs of resources used to implement the intervention, including training, staff and travel costs; family or household costs (resources related to food shopping and activities); and health care resources. One of the aims of the project is to undertake economic evaluation to evaluate the effectiveness of the proposed intervention for parents or carers from disadvantaged backgrounds, in preventing unhealthy weight gain in children aged 5 to 11 years living in the same household. This requires data linkage to Medicare funded services and dispensing of subsidised pharmaceuticals to capture total health care expenditure and out-of-pocket costs (Services Australia RMS1190). All analyses will be adjusted for clustering and all participant data will be de-identified prior to analysis.

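### The satisfaction-with-intervention questionnaire sits in the face-to-face survey, and so can reveal the arm to the field workers who are said to be blind and who take the outcome measurements

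*Protocol article*

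**What the plan says.** Four sections of the protocol article bear on this.

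- **Assessment, primary outcome.** The child's anthropometric data "will be measured at 0, 10 and 60 weeks by bilingual field workers".
- **Assessment, parent data.** Parents or carers "will participate in a face-to-face interview with trained bilingual field workers to collect data on family functioning" and several other secondary domains. A list of instruments follows, introduced by "The following outcome measures will be collected via face-to-face survey using Qualtrics software". Its last entry is the "Participant Evaluation Questionnaire as a composite measure to assess satisfaction with intervention".
- **Blinding.** Field workers are blinded and "will therefore have no knowledge of which group (intervention or control) the participating parent- or carer-child dyad has been allocated to". No time limit is attached. The section adds that group facilitators and research staff do not collect data.
- **Control group.** Control families do not receive the program; they have usual care.
- **Statistical analysis.** A different mode is given for the parent questionnaires: "Parents will respond to self-administered questionnaire on family functioning, feeding related parenting" and further domains. The satisfaction form is not among the domains named there.

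**The concern.** A satisfaction form about the program has meaningful answers only in the intervention arm. If a field worker administers it, or is present while it is completed, the worker learns the arm. If controls are asked as well, their answers show that they had no program.

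Blinding of the field workers matters in this trial. Parents know their arm, and most secondary outcomes are parent reports given to an interviewer. The same staff group measures the height and weight from which the primary outcome, BMIz, is calculated. Allocation by postcode adds a further route: a worker who learns one family's arm, and knows that allocation is by postcode, can infer the arm of other families at that postcode.

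**Working it through.** No plan figure is in question and no formula applies. The check is whether the statements can all hold together.

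1. **Who measures the primary outcome?** Bilingual field workers, at 0, 10 and 60 weeks (Assessment).
2. **Who runs the face-to-face survey?** The sentence introducing the list names no collector. The sentence before it gives the parent interview to field workers. The Blinding section rules out facilitators and research staff. No other staff group is named as collecting data, so field workers are the only reading the text leaves open.
3. **Is the satisfaction form in that survey?** Yes, as the last item on the list. Nothing in the text assigns it to a separate person or places it after the last anthropometric measurement.
4. **Do its answers identify the arm?** Yes. Only intervention families have a program to rate (Control group).
5. **Does the blinding statement allow for this?** No. "All bilingual field workers will be blinded to randomisation and will therefore have no knowledge of which group" a dyad belongs to, with no exception for follow-up visits.
6. **Does the self-administered wording remove the conflict?** No. It disagrees with the face-to-face wording for the domains that both sections cover, and it does not mention the satisfaction form.

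Steps 1 to 4 together contradict step 5.

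**Reach of a disclosure.** It depends on the order of events:

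| When the form is given | Same family | Other families in the postcode |
|---|---|---|
| Before other measurements at a visit | The rest of that visit, and later visits if the same worker returns | Later visits by that worker |
| After all measurements at week 10 | Week 60 only, if the same worker returns | Later visits by that worker |
| After all measurements at week 60 | None | Later visits by that worker, if any remain |

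The text gives neither the timepoint nor the order, and the schedule in Fig. 1 is not available here, so the row that applies is unknown. For scale, the average planned cluster is 800 / 92 = 8.7 families per postcode if all 92 postcodes recruit. That is a cluster size, not a count of families unblinded.

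**The case against.** The strongest reply is that the link to field workers is an inference. The interview sentence names its domains, and satisfaction is not one of them; the list sentence names no collector. Outcome data are recorded on a tablet (Equipment), so a parent could complete a form privately during a visit, which would fit both descriptions of the mode. A journal article may also leave such logistics to a field manual. This lowers certainty about what will happen in practice. It does not remove the conflict, because the article makes positive statements that disagree and excludes the other staff who might have collected the form.

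Three further points stand and limit the concern:

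- Blinding is not the only safeguard. The Assessment section also provides a standardised measurement protocol, training, and a height and weight guide, and the Equipment section specifies digital scales.
- A disclosure spreads through a postcode only as far as one worker's later visits. Each family is assigned a bilingual field worker, so families in a multilingual postcode may be divided among workers.
- Moving the form does not secure blinding by itself. Parents know their arm and may mention it at any visit.

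**Conclusion.** The point holds as an internal contradiction with a practical consequence. As written, the satisfaction form can reveal the arm to the staff who measure the primary outcome and interview parents. It rests on two readings of the text: that field workers run the whole face-to-face survey, and that no unstated exception exists for this form.

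The exposure is any measurement taken after the form in that family, plus later visits by the same worker to other families in the postcode. Parent-reported outcomes collected by interview are probably more exposed than scale and stadiometer readings, though the document gives no figure for either.

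Two stronger conclusions that a reader might infer are not supported:

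- **That blinding is lost for all data from week 10 onward.** The timepoint and order of the form are not stated, and the text does not say whether the same worker returns. Blinding can be lost from that point; it need not be.
- **That the bias is a large share of the target effect.** Suppose a 0.5 cm differential height reading at 130 cm and a BMI of 17: 2 × 0.5 / 130 = 0.77%, and 0.0077 × 17 = 0.13 kg/m². At 2 to 2.5 kg/m² per z unit this is 0.05 to 0.07 BMIz, or about 35% to 44% of the 0.15 target. The arithmetic is right, but every input except the 0.15 is an assumption. It would also need an average misreading of 0.5 cm in one direction between arms, which nothing in the document suggests.

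The size of any bias therefore remains undetermined. The change is worth making because it is cheap and removes a disclosure that the plan itself creates.

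**What to change.** 1. Take the Participant Evaluation Questionnaire out of the field-worker visit. Send it to intervention families as a self-completed Qualtrics or REDCap link. Do not have it collected in a facilitator-led session, because the Blinding section keeps facilitators out of data collection.
2. Require height and weight to be taken before any questionnaire at every visit.
3. Reconcile the Assessment section (face to face) with the Statistical analysis section (self-administered), and state for the satisfaction form who handles it, by what mode and when.

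The cost is one survey link, a line in the field-worker manual and a correction to the text. The downside is a somewhat lower response to the satisfaction form.
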